#### Intervention: Enhanced Academic Support (EAS)

Families allocated to the intervention group are assigned a practitioner with training in EAS. EAS is delivered as described in the “Methods and design” subsection “Intervention”.

#### Comparison condition: business as usual (BAU)

Families allocated to the BAU group are assigned a practitioner without training in EAS. BAU is delivered as described in the “Methods and design” subsection “Comparison condition (business as usual)”.

#### Post-assessment

Six months after pre-assessment, the post-assessment is administered. A selection of participating families will be invited to semi-structured interviews, and a selection of participating practitioners and other stakeholders will be invited to participate in focus group interviews.

#### Follow-up assessment

Six months after post-assessment, the follow-up assessment is administered.

### Statistical analyses

We will consider efficacy for each of the primary outcomes. In other words, efficacy will be gauged in an outcomes-specific manner. A significance level of .05 will be used.

Outcomes will be evaluated using analysis of covariance (ANCOVA), controlling for baseline scores and covariates. Children’s age, implementation drivers, children’s mental health, social skills, and executive functions will be tested in regression models, as will possible subgroup analyses. To test for indirect effects (or mediation), models will be tested in a structural equation modeling (SEM) framework. Indirect effects variables include PASS, Five-to-Fifteen , and the end-of-intervention checklist measures. Implementation drivers as predictors of outcomes will be tested in regression models. We will evaluate effectiveness in two parts. The pre-post outcome analysis will use ANCOVA with baseline measures and covariates as control variables. We will test intervention effects including all data waves in SEM. See Figs. 2 and 3 for the theory of intervention change depicting variables included in the analyses.

We will examine and present data both in intention-to-treat (ITT) and as-treated (AT) designs, as the two approaches answer different questions. An ITT design answers the question “Does the intervention make a difference?” An AT analysis, on the other hand, answers the question “What are the effects likely to be if the client (or family) is exposed to the intervention?” We consider both of these questions important. This procedure has been recommended as best practice [46].

We will use multiple imputation for missing values for the pre-post ANCOVA in an ITT design. In the SEM models, missing data will be estimated using full information maximum likelihood.

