### Aims and hypotheses

The present study has three overarching aims:To evaluate the feasibility of the IKT-K model designed to develop, implement, and evaluate empirically supported practice in CWSTo evaluate the effects of the intervention, EAS, on children in CWS and their familiesTo explore associations between implementation drivers (readiness, climate, fidelity) and outcomes for children and families.

The following research questions will be examined to evaluate Aim 1:To what degree are the core components of EAS implemented in the CWS?What adaptations are made to the core components of EAS?What are stakeholders’ perceptions of the IKT-K model’s feasibility and usefulness, as assessed in focus groups?To what degree are climate for implementing evidence-based practice (EBP) and susceptibility for change of practice (readiness for change) associated with intervention fidelity in the CWS?To what degree will practitioners in the experimental group increase their perceived competence in delivering academic support to children and families from pre- to post-intervention?To what degree is adherence to core components of EAS associated with academic achievement and parental involvement for families in the EAS group?

The following hypotheses will be tested to evaluate Aims 2 and 3:Children in families who receive the EAS intervention will improve their academic achievement relative to children and families in a parallel, active comparison group who receive “business as usual” (BAU) support.Parents who receive the EAS intervention will increase their engagement in their children’s school situation relative to parents who receive BAU.Intervention effects will be moderated by child age, readiness for change, and climate for implementing EBP.Covariates include children’s mental health, social skills, and executive functioning scores, as well as child gender and pre-intervention academic performance (math and reading) and parental involvement.Intervention effects (measured by academic performance tests and parental involvement) are associated with climate for implementing EBP and readiness for change.More adherence to EAS principles will be positively associated with academic achievement and parental involvement for families in the EAS group

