## Methods and design

This study is a randomized controlled pragmatic trial conducted in three ordinary child welfare agencies in and around Oslo, Norway. The agencies differ in size, organizational structure, and demographic characteristics. Selected practitioners at each site have received training in the EAS intervention. Practitioner selection to EAS training was mostly a matter of practicality (i.e., half of the practitioners in a team, geographic area, or unit were selected by their managers to receive training). Participating families are recruited individually at each site and randomized either to an EAS-trained practitioner or to a practitioner not trained in EAS who is delivering regular child welfare support measures (BAU). EAS is delivered over the course of 6 months. Participants are assessed before and immediately after EAS, and at follow-up, 6 months after the end of the intervention. The schedule of recruitment, allocation, assessments, and experimental conditions is provided in Fig. 1. The Standard Protocol Items: Recommendations for Interventional Trials (SPIRIT) checklist is provided as Additional file 1.

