#### Randomization

At the time of consent, parents and children are informed that they will be randomly allocated to one of two conditions; one group, the BAU condition, receives regular measures from CWS, whereas the experimental condition receives the EAS intervention in addition to a regular child welfare measure. Blinding is not possible in this study; child welfare practitioners who have received EAS training will exclusively give EAS to study families, and parents and children will most likely understand to which group they have been assigned.

After completing the pre-assessment, participants are automatically randomized to either the intervention group (EAS) or the comparison group (BAU). A computer software (Confirmit) generates a random numbers table to assign random numbers to participants within blocks. A block randomization with a block of 10 is used, and randomization is carried out site-wise. The research coordinator informs the team manager at the site to assign the case to a practitioner with or without EAS training. All edit trails in Confirmit are recorded. Outcome assessors are blinded to allocation. In-depth technical details can be provided upon request.

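### The stated ANCOVA names neither site (the randomisation stratum) nor practitioner (the delivery cluster within arm); site costs precision, and practitioner understates standard errors by an amount the documents do not fix

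*Protocol article*

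**What the plan says.** **Model.** The Statistical analyses section gives the model twice: "Outcomes will be evaluated using analysis of covariance (ANCOVA), controlling for baseline scores and covariates", and again "The pre-post outcome analysis will use ANCOVA with baseline measures and covariates as control variables". A second part uses structural equation models (SEM) on all data waves.

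**Covariates.** Aims and hypotheses lists children's mental health, "social skills, and executive functioning scores, as well as child gender and pre-intervention academic performance (math and reading) and parental involvement". Site and practitioner are not on that list. In the statistical text, site appears only as a subgroup factor (Power calculation).

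**Stratum.** Under Randomization: "A block randomization with a block of 10 is used, and randomization is carried out site-wise". Methods and design says of the three sites: "The agencies differ in size, organizational structure, and demographic characteristics".

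**Delivery cluster.** "Participating families are recruited individually at each site and randomized either to an EAS-trained practitioner or to a practitioner not trained in EAS" (Methods and design). After allocation, "The research coordinator informs the team manager at the site to assign the case to a practitioner with or without EAS training" (Randomization). No practitioner therefore serves both arms. The section on the comparison condition adds that usual support differs between individual practitioners.

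**Sample size.** Power calculation gives 39 families per group, 78 in all, for d = 0.65 and power 0.80, and recruits 120. The reasons given for the increase are uncertainty in the calculation, subgroup analyses, dropout and non-normal scores. Clustering is not among them.

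**The concern.** An analysis should reflect how families were allocated and how treatment was delivered. Two features of this design are missing from the stated model.

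- **Site.** Blocking within site balances the arms across agencies. If the model has no site term, between-site variation stays in the residual, the standard error of the arm effect is too large, and the precision gained by stratifying is lost.
- **Practitioner.** Families with the same practitioner share that person's skill and style, so their outcomes may be correlated. Because practitioners are nested within arm, this correlation feeds directly into the variance of the arm contrast. A single-level ANCOVA ignores it and gives standard errors that are too small.

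The second omission is the one that could produce a false positive. It bears on reading, mathematics and parental involvement alike.

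**Working it through.** **1. Reproduce the plan's figure.** Inputs from Power calculation: d = 0.65, power 0.80, equal groups. A two-sample t-test at two-sided alpha 0.05 needs 38.14 per group, rounded up to 39, so 78 in all. (Alpha is printed there as 0.5, which would give 11 per group under a two-sided normal formula; 78 follows only from 0.05, the level given in Statistical analyses.) The calculation uses independent families, so 78 carries no clustering allowance.

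**2. Families per practitioner.** The documents give no count. The only indirect figure is about 50 handbooks (Table 2), a rough upper guide to the number of EAS practitioners: 60 / 50 = 1.2 families each. Assumed alternatives are 30, 20 and 15 practitioners per arm, that is m = 2, 3 and 4, with equal caseloads and the same number in both arms. The ICC is also not given; 0.05 to 0.10 is assumed.

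**3. Effect of ignoring practitioner.** Design effect DE = 1 + (m − 1) × ICC. True type I error = 2 × [1 − Φ(1.96 / √DE)]. Adjusted sample size = 2 × (39 × DE, rounded up). Power is at N = 120 with d = 0.65 and complete data.

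| m | ICC | DE | √DE | Type I error | 78 becomes | Power at 120 |
|---|---|---|---|---|---|---|
| 1.2 | 0.05 | 1.01 | 1.005 | 0.051 | 80 | 0.94 |
| 1.2 | 0.10 | 1.02 | 1.010 | 0.052 | 80 | 0.94 |
| 2 | 0.05 | 1.05 | 1.025 | 0.056 | 82 | 0.94 |
| 2 | 0.10 | 1.10 | 1.049 | 0.062 | 86 | 0.92 |
| 3 | 0.05 | 1.10 | 1.049 | 0.062 | 86 | 0.92 |
| 3 | 0.10 | 1.20 | 1.095 | 0.074 | 94 | 0.90 |
| 4 | 0.05 | 1.15 | 1.072 | 0.068 | 90 | 0.91 |
| 4 | 0.10 | 1.30 | 1.140 | 0.086 | 102 | 0.88 |

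Example, last row: DE = 1 + 3 × 0.10 = 1.30; 39 × 1.30 = 50.7, rounded up to 51, so 102 in all. Even at m = 6 and ICC 0.10 (DE 1.50) the requirement is 118 and power at 120 is 0.83.

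**4. Effect of ignoring site.** Simulation: 8,000 runs per setting, 120 families, three equal sites, blocks of 10 within site, no baseline covariates, no practitioner effect. With a site share of outcome variance of 0.05 or 0.10, the model without site rejects in 0.047 or 0.040 of runs, and the model with site in 0.050 or 0.047. The Monte Carlo standard error is √(0.05 × 0.95 / 8000) = 0.0024, so the loss is small at 5% and clearer at 10%.

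**5. Both together.** Same simulation with a site share of 0.05 and practitioner effects added. The last column omits both terms, as the stated model does.

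| Practitioners per arm | ICC | Site in model, practitioner ignored | Both ignored |
|---|---|---|---|
| 30 | 0.05 | 0.056 | 0.053 |
| 30 | 0.10 | 0.061 | 0.057 |
| 15 | 0.05 | 0.069 | 0.066 |
| 15 | 0.10 | 0.087 | 0.080 |

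The middle column agrees with the formula in step 3. Omitting site offsets part of the inflation, not all of it.

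**The case against.** **This is a condensed article.** The covariate list is introduced as an inclusion, not closed. The text refers to Figs. 2 and 3 for the variables analysed, and neither is shown. Stratum terms and standard-error methods often sit in an analysis plan. This stands in part: one cannot say that site and practitioner are excluded. But the article goes as far as naming the model, the covariates, the analysis sets and the missing-data methods, and nothing in the text or captions points to either term.

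**The one figure with a source in the documents is negligible.** About 50 handbooks gives a design effect of 1.01 to 1.02 at ICC 0.05 to 0.10. The Exclusion criteria section counts 160 managers and practitioners in the study, which also does not suggest that very few carry the cases. This stands, and it is why the finding is not graded higher. The protocol does not, however, state or guarantee such an even spread, and unequal caseloads would raise the design effect.

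**Power is not threatened.** This stands for d = 0.65 over the ICC range used, although the 42 extra families (120 − 78) must also cover dropout and subgroup analyses.

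**Stronger readings that a reader might infer.** One is that the confidence interval for every primary outcome is materially wrong. The documents do not support that: omitting site only makes the test conservative, and the practitioner effect may be close to nil. Another is that the error rate doubles to about 10%. That needs four families per practitioner and an ICC of 0.15 at once, and the documents give neither.

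**Conclusion.** The concern holds in a limited form. The stated primary analysis names neither the stratum nor the delivery cluster, and 78 assumes independent families. Omitting site gives a type I error of about 0.040 to 0.047 for a site share of 5 to 10% of the remaining variance: a loss of precision, not a false-positive risk. Omitting practitioner gives about 0.051 to 0.052 at 1.2 families per practitioner and 0.056 to 0.086 at 2 to 4. These figures rest on an assumed ICC of 0.05 to 0.10, equal caseloads and 60 families per arm; only the 1.2 has even a rough source in the documents.

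Managers chose which practitioners were trained, so a reader might also infer that modelling practitioner would remove any resulting bias. It would not: a random intercept corrects the standard error, and systematic differences between trained and untrained practitioners stay in the arm contrast. That belongs among the stated limitations.

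Severity: should be fixed. Confidence: moderate.

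**What to change.** Before outcomes are analysed:

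1. Add site as a fixed effect (three levels) in the ANCOVA and the SEM.
2. Account for practitioner in the ANCOVA with a random intercept and small-sample degrees of freedom (Satterthwaite or Kenward-Roger). If most practitioners have only one family, the variance component is barely identifiable; use small-sample cluster-robust standard errors instead, and state in advance how the choice is made.
3. Use practitioner-clustered standard errors in the SEM.
4. Define the cluster as the practitioner first assigned after randomisation, because Table 2 foresees staff turnover.
5. Report the number of practitioners and families per practitioner in each arm, and the estimated ICC.
6. State that 78 carries no clustering allowance, and that 120 largely absorbs a plausible design effect for d = 0.65.
7. List manager selection of trained practitioners as a limitation that the model does not remove.

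Cost: wording in the analysis plan, a record of which practitioner each family was assigned to, two degrees of freedom for site, and possibly slightly wider intervals. If the practitioner variance is zero, the mixed model reduces to the ANCOVA with site.

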#### Power calculation

The study aims to recruit 120 families. The intervention under study is newly developed; hence, we used a meta-analysis testing the overall effect of similar interventions (targeting parental involvement in children’s learning, including “paired reading”) to inform the required sample size. The outcomes used to assess effect sizes in the meta-analysis were a combination of different standardized and unstandardized reading measures. The suggested effect sizes were in the range of *d* = .65 to 1.15 [22]. With α < 0.5, power = 0.80, and expected effect size *d* = .65, the necessary sample size is *n* = 78, with 39 families in each group. Although the Oral Reading Fluency (ORF) test administered in the current trial is similar to the assessments used by the studies in the meta-analysis, none of those studies used the actual ORF test of this trial. Hence, the power calculation lacks some precision. To account for uncertainty in the power calculation, subgroup analyses (of gender, site, and CWS measure), and possible study dropouts, and to compensate for the possibility of non-normal distribution of scores, more participants than deemed necessary according to the power calculation were recruited. Based on information from the participating CWS agencies about their target groups, this sample size seems attainable.

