Each of the visits consists of specific actions and activities (practice elements) for the practitioners and the families to engage in together. Practitioners are also instructed on how these actions and activities ought to be carried out (process elements). Important implementation elements such as ongoing support, local tailoring, and intervention flexibility are integrated into the delivery of the intervention. Even though core components are assigned to separate sessions, and practice and process elements are clearly described, flexibility within fidelity is encouraged. This means that practitioners can adapt the sequence of components, emphasis on components, combinations of components, and time between sessions as they see fit, as long as they adhere to the practice and process elements of the core components and report adherence, dosage, and adaptations in the monitoring checklists after each session (see the section “Monitoring and safety”). Additionally, pre-defined component-specific adaptations that are likely to be useful in different settings and scenarios are described and encouraged in training and in the handbook.

EAS is designed to be a flexible supplement to the support that families in CWS already receive. Hence, EAS is delivered in addition to the family’s child welfare measure. The practitioners are free to combine EAS sessions with other measures or help they provide, or they can deliver EAS in separate sessions with the family. A session usually varies in length from 30 to 120 min. The session length is monitored.

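### As-treated results are presented unranked beside ITT and said to answer the exposure question, although that contrast is not randomised and is open to selection bias

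*Protocol article*

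**What the plan says.** The Statistical analyses section commits to two analysis sets: "We will examine and present data both in intention-to-treat (ITT) and as-treated (AT) designs, as the two approaches answer different questions". ITT is given the question of whether the intervention makes a difference. As-treated is given this one: "What are the effects likely to be if the client (or family) is exposed to the intervention". The section then adds "We consider both of these questions important" and cites a source for the practice.

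The outcome model is described once, without distinguishing the two sets: "Outcomes will be evaluated using analysis of covariance (ANCOVA), controlling for baseline scores and covariates". Missing data are handled for one set only: "We will use multiple imputation for missing values for the pre-post ANCOVA in an ITT design".

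Other sections bear on who receives EAS:

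- **Stopping rules.** The reasons for discontinuation include the end of the family's child welfare measure, out-of-home placement or loss of custody, conditions such as abuse or acute suicidality coming to light, and withdrawn consent.
- **Randomization.** After allocation, a team manager assigns the practitioner.
- **Intervention.** Delivery is flexible: "practitioners can adapt the sequence of components, emphasis on components, combinations of components, and time between sessions as they see fit". Exposure is therefore not a fixed quantity.

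The article does not define as-treated, gives no expected uptake, and does not say which of the two results governs the conclusion.

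**The concern.** An as-treated analysis groups families by what they received, not by what they were allocated. Several of the protocol's own reasons for stopping plausibly go with a worse outlook for the child. Families who receive EAS as intended may therefore differ from those who do not, for reasons unrelated to EAS. Families, practitioners, agencies and custody decisions all play a part in this.

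Such a contrast does not in general estimate the effect of exposure, yet the article says that it answers that question. With no ranking and no caveat, a null ITT result beside a positive as-treated result would leave readers without guidance, and selection alone could produce that pattern.

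**Working it through.** **The plan's own figure.** The article gives no number on this point. The nearest is the sample size: "With α < 0.5, power = 0.80, and expected effect size *d* = .65, the necessary sample size is *n* = 78, with 39 families in each group". A two-sided t-test at 0.05 with d = 0.65 and 80% power needs 38.14, so 39 per group, or 78 in total, which reproduces it. Taking 0.5 literally gives 11 per group, so the printed value is evidently a slip for 0.05. The analysis section agrees: "A significance level of .05 will be used". I use two-sided 0.05 below.

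**Inputs from the article.** 120 families; ANCOVA on baseline scores and covariates.

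**Assumed inputs, not in the article:**

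- 60 families per arm.
- No true effect.
- A share p = 0.6 to 0.8 of the EAS arm completes EAS, and non-completers are counted with the comparison group.
- Family functioning F correlates ρ = 0.3 to 0.5 with a normal latent tendency to complete.
- F correlates 0.5 with the outcome, so it explains 25% of outcome variance.

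**Unadjusted bias.** With φ the normal density at the completion cut-point:

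bias = 0.5 × ρ × φ × [1/p + 1/(2 − p)]

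SE = √[1/(60p) + 1/(120 − 60p)]

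| p | ρ | φ | Bias (SD) | SE | Two-sided rejection |
|---|---|---|---|---|---|
| 0.8 | 0.3 | 0.280 | 0.5 × 0.3 × 0.280 × 2.083 = 0.09 | 0.186 | 8% |
| 0.6 | 0.5 | 0.386 | 0.5 × 0.5 × 0.386 × 2.381 = 0.23 | 0.199 | 21% |

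**Bias after adjusting for baseline score.** Further assumptions: F also correlates 0.5 with the baseline score, and the pre-post correlation r is 0.6 to 0.8. Let c = 0.5ρφ, the covariance of F with as-treated status, and v = (p/2)(1 − p/2), the variance of that status.

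bias = 0.5c(1 − r) / (v − 0.25c²)

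The SE shrinks by about √(1 − r²).

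- p = 0.8, ρ = 0.3, r = 0.8: c = 0.042, v = 0.24, bias = 0.0042/0.2396 = 0.02 SD. SE is 0.112 and rejection about 5%.
- p = 0.6, ρ = 0.5, r = 0.6: c = 0.0966, v = 0.21, bias = 0.0193/0.2077 = 0.09 SD. SE is 0.160 and rejection about 9%.

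A simulation of 1,000,000 families at each of these two corners agreed with both formulas to within 0.002 SD. The ITT difference in the same simulations was zero to within 0.002 SD.

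**When baseline does not capture the selection.** Suppose a share q of the EAS arm does not receive EAS, and receivers exceed non-receivers by g SD after all covariates, for instance because of a crisis during the trial. Then bias = 2qg/(1 + q):

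| q | g (SD) | Bias (SD) | Two-sided rejection |
|---|---|---|---|
| 0.1 | 0.25 | 0.05 | 6% |
| 0.2 | 0.5 | 0.17 | 15% |
| 0.3 | 0.8 | 0.37 | 49% |

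Rejection here uses a residual SD of 1. As q goes to zero, so does the bias. ITT has no bias in any of these scenarios, given complete outcome data.

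**The case against.** The case on the other side has real force.

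- **Adjustment is planned.** Unadjusted figures do not describe the planned ANCOVA. This stands: if selection acts only through stable functioning that relates equally to baseline and outcome, bias falls to 0.02–0.09 SD and false positives to 5–9%. It does not cover unmeasured factors or events after baseline.
- **As-treated is not defined.** Counting non-completers with the comparison group is an assumption. The article speaks of exposure, not completion. If any EAS session counts as exposure, non-receipt could be small and the bias negligible. This also stands. The definition may sit in an analysis plan that is not shown, and its absence is not the finding.
- **Equal standing is partly inferred.** ITT is given the efficacy question, and multiple imputation is specified only for the ITT ANCOVA. A reader might infer that a positive as-treated result would by itself be claimed as efficacy, or that the as-treated result is certain to be biased. The article supports neither: it contains no such decision rule and no uptake figure.
- **A complier-average effect has assumptions too.** It requires that allocation affects outcome only through EAS. Here allocation also changes the practitioner who gives the family's regular support. This limits the alternative and has to be stated with it.
- **The practice is cited as recommended.** The source is not available here and cannot be weighed. Showing as-treated beside ITT is not in itself an error.

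What survives is the positive statement that as-treated answers the exposure question, made without rank or caveat. A later plan could rank the two analyses, but that statement would still need correcting.

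**Conclusion.** The concern holds as a fault of interpretation and ranking. The as-treated contrast is not protected by randomisation, the protocol's own stopping reasons give a plausible route to selection, and the article attaches a causal reading to the contrast without a warning.

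The size cannot be fixed from the document. The ranges above rest on assumed completion, assumed links between functioning and completion, an assumed pre-post correlation and an assumed as-treated definition. For the planned adjusted analysis, 0.02–0.09 SD is the better illustration if selection is through stable functioning. The 0.09–0.23 SD range ignores the adjustment and should not be read as the expected bias of the planned model. Selection through events during the trial could give more, and near-complete uptake would give almost none.

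Because ITT is retained, the trial's main comparison is not damaged. The change should be made, but it does not threaten the design.

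**What to change.** 1. State that the ITT analysis alone governs the efficacy conclusion for each primary outcome.
2. If as-treated results are kept, define the groups in advance, label the analysis descriptive or supportive and non-randomised, and remove the statement that it answers the exposure question.
3. Address that question with a complier-average causal effect, using randomised arm as the instrument and receipt of any logged EAS session as exposure. Counting any session limits the problem of partial exposure. The estimate can be obtained by two-stage least squares or within the planned structural equation framework.
4. State the exclusion assumption, and its limit: arm also determines which practitioner delivers regular support.

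The cost is mainly wording, since practitioners already complete a checklist after every session. The complier-average standard error is roughly the ITT standard error divided by uptake, so at 80% uptake the interval is 1/0.8 = 1.25 times as wide, about 25% wider. The estimate is scaled by the same factor, so this analysis adds no power over ITT.
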